### Clinical and laboratory evaluations

The physical examination, laboratory evaluations, and medication reviews will be conducted before treatment; the laboratory evaluations will include a complete blood count, serum electrolytes, blood urea nitrogen, creatinine, calcium, phosphorous, protein, albumin, and glucose; a liver function test; a thyroid function test (TFT); rapid adrenocorticotropic hormone (ACTH) test (basal cortisol, ACTH, cortisol at 30 min and 60 min), serum osmolality; urinalysis, urine electrolytes, urine osmolality. sNa levels will be measured every 6 h for 2 days [30]. The GCS score will be assessed before treatment and at 24 and 48 h of treatment. All types and volumes of administered fluid during 48 h will be monitored.

### Safety issues

All adverse events related to overcorrection will be recorded and followed up during the study period or until resolution during treatment with 3% hypertonic saline. Any serious adverse events will be reported to investigators and the Ethics Committee. We will check for overcorrection at every sample time point and conduct relowering treatment as needed. Relowering treatment is performed as follows if the achieved sNa level is ≥10 mmol/L at any sample time point within the first 24 h or if the achieved sNa level is ≥18 mmol/L at any sample time point within 48 h: discontinuing ongoing active treatment; initiating infusion of 10 mL/kg of 5% dextrose over 1 h; and/or adding desmopressin 2 mcg [1].

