## Background

Hyponatremia is the most common electrolyte imbalance encountered in clinical practice, and is associated with increased mortality and length of hospital stay [1]. The symptoms related to hyponatremia span a broad range from moderately severe (cognitive test abnormalities, gait impairment) to severe or life-threatening (hypoxemia, coma, and epilepsy) [2–5]. Treatment strategies for hyponatremia differ according to the severity of clinical symptoms and duration of hyponatremia [6]. The extent and rate of increase in serum sodium (sNa) levels during treatment are crucial. Overcorrection of chronic hyponatremia may result in osmotic demyelination syndrome (ODS), whereas undercorrection may be insufficient to prevent its life-threatening manifestations [6–9].

Several methods for continuous infusion of hypertonic saline have been used to guide the rate of fluid administration to achieve the required sNa target [10, 11]. The increase in sNa should be limited to 8–10 mmol/L within the first 24 h and 18 mmol/L within 48 h [11, 12]. As these methods were based on static models of a dynamic clinical situation, they had a bias toward overcorrection of hyponatremia [1, 13–15].

Recent guidelines have recommended prompt infusion of 100–150 mL of 3% saline over 10–20 min to increase the sNa by 4–6 mmol/L during the first hour. A pragmatic approach to treatment with hypertonic fluid is to use small, fixed boluses to achieve controlled incremental increases in sNa [1, 13–17]. However, this recommendation was the result of small randomized trials [18], case reports with small numbers of patients [14, 19], and expert opinion [20–23]. No high-quality evidence has been reported regarding whether hypertonic saline is best administered as a continuous infusion (preferred by most) or as a rapid intermittent bolus injection. The purpose of the present study was to investigate the efficacy and safety of rapid intermittent correction compared with slow continuous correction with hypertonic saline in patients with symptomatic severe hyponatremia. Furthermore, the study will examine prevailing conceptions regarding the optimal treatment of severe symptomatic hyponatremia.

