### Study design

This study is a prospective, investigator-initiated, multicenter, open-label, randomized controlled study with two experimental therapy groups. We have followed the Standard Protocol Items: Recommendations for Interventional Trials (SPIRIT) 2013 Statement which defines standard protocol items for clinical trials [24] (see Additional file 1). The study algorithm is depicted in Fig. 1 and the SPIRIT and study schedule are given in Figs. 2 and 3. After enrollment, clinical follow-up will be performed 2 days after treatment with 3% hypertonic saline.

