### Outcome measures

The primary outcome is the incidence of overcorrection, a surrogate marker of ODS, at any given period, defined as follows: increase in sNa level by >12 mmol/L within the first 24 h or increase in sNa level by >18 mmol/L within 48 h. The secondary outcomes will include efficacy and safety; changes in symptoms between pretreatment and 24 and 48 h after treatment with 3% hypertonic saline; time from treatment initiation to an increase in sNa ≥5 mmol/L; time from treatment initiation to the achievement of a sNa >130 mmol/L; incidence of target correction rate, defined as an achieved sNa <10 mmol/L within 24 h and a sNa <18 mmol/L within 48 h; length of hospital stay; incidence of additional treatment; incidence of ODS confirmed by the *International Classification of Disease, 10th Revision (ICD-10)* code or magnetic resonance imaging (MRI); incidence of relowering treatment; and change in GCS score between pretreatment and 24 and 48 h after 3% hypertonic saline treatment.

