### Statistical analyses

Statistical analyses will be performed on both per-protocol (PP) and intention-to treat (ITT) bases. For the PP analysis, all participants who completed the study will be included to evaluate the primary and secondary outcomes. For the ITT analysis, all participants who were enrolled and randomized to one of the two groups will be included. The baseline characteristics and laboratory data will be presented as means and standard deviations for continuous variables and as frequencies and percentages for categorical variables.

The incidence of overcorrection, ODS, relowering treatment, and target correction rate (achieved sNa <10 mmol/L within the first 24 h and sNa <18 mmol/L within 48 h) will be compared between the two groups using a *χ*
^*2*^ test and Fisher’s exact test. In interim analysis, if the *P* value < 0.003 then we would stop the study early for significance of outcome. If not, we would recruit another half of subjects. The differences in changes in symptoms and GCS scores between pretreatment and 24 and 48 h, time to reach target sNa, time to achieved sNa ≥5 mmol/L for the first time, and length of hospital stay will be analyzed using Student’s *t* test or the Mann-Whitney *U* test. A value of *P* < 0.05 will be considered statistically significant. All analyses will be performed using SPSS Statistics software V21.0 (IBM Corporation, Armonk, NY, USA).

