### Data and safety monitoring

The paper data collection sheets and signed informed consents will be stored in a locked cabinet, and the electronic data base will be stored on password-protected secure severs. Any unanticipated adverse events that occur during the study will be reported to the Institutional Review Board in accordance with the procedures of Seoul National University Bundang Hospital, Korea. For any revised study procedure, the modification will be submitted to the Seoul National University Bundang Hospital Institutional Review Board for approval and to ClinicalTrials.gov. The data will be kept confidential with only limited access to research investigators.

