We will also include the participants with chronic hyponatremia. It is well-known that using a threshold of 48 h is frequently applied to distinguish “acute” from “chronic” hyponatremia [1]. Because not all patients have sNa measured within 48 h prior to visiting the emergency room. Therefore, it is practically impossible to exclude the patients with chronic hyponatremia based on these definitions. Second, the most important factor in determining treatment of hyponatremia is the presence of symptoms, irrespective of biochemical degree or timing (acute versus chronic) of hyponatremia [1]. We will enroll the patients with moderately severe to severe symptoms who need to be treated. In other words, even if the patients belong to the chronic hyponatremia group, the patients with symptomatic hyponatremia need to be treated. Therefore, we thought that including the patients with chronic hyponatremia is reasonable and inevitable.

We will use the overcorrection rate as a primary outcome. ODS is a serious complication, which should be prevented for patient safety, and it is one of the critical outcomes in the management of hyponatremia, but it is difficult to diagnose and very uncommon [1, 31]. Several studies have reported that the rate of overcorrection is strongly correlated with ODS, and is highly sensitive for predicting ODS. In terms of safety issues, the overcorrection rate might be a good laboratory outcome in our trial [1, 15, 32, 33].

This trial may have some limitations. We will enroll patients who visit the emergency room in general hospitals; therefore, patients with hospital-acquired hyponatremia will be excluded. Second, various situations may affect protocol violations, considering that on-duty physicians and nurses may work in shifts. For this, reason we made both protocols as simple as possible.

In summary, the SALSA study is the first prospective, multicenter, randomized, open-label, controlled clinical trial to evaluate the clinical usefulness of rapid intermittent correction management in patients with moderately severe or severe hyponatremia. The aim of this study is to evaluate the efficacy and safety of rapid bolus correction compared with slow continuous correction of hyponatremia.

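### The adverse-event rule covers events related to overcorrection; non-serious, expected events with another cause have no stated route into the safety comparison

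*Protocol article*

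**What the plan says.** The recording rule stands in Safety issues: "All adverse events related to overcorrection will be recorded and followed up during the study period", or until they resolve. Two further sentences reach beyond overcorrection. The next sentence of the same section reads "Any serious adverse events will be reported to investigators and the Ethics Committee", and Data and safety monitoring adds "Any unanticipated adverse events that occur during the study will be reported to the Institutional Review Board".

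Under Outcome measures, "The primary outcome is the incidence of overcorrection, a surrogate marker of ODS, at any given period". The secondary list adds symptom change, GCS change, time to a sodium rise of at least 5 mmol/L, time to sodium above 130 mmol/L, target correction rate, length of stay, additional treatment, osmotic demyelination syndrome (ODS) and relowering. Statistical analyses names the binary outcomes to be compared between groups: "The incidence of overcorrection, ODS, relowering treatment, and target correction rate". It names no comparison of adverse events in general.

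On design, "This study is a prospective, investigator-initiated, multicenter, open-label, randomized controlled study with two experimental therapy groups". On purpose, the Discussion closes with "The aim of this study is to evaluate the efficacy and safety of rapid bolus correction compared with slow continuous correction of hyponatremia", and its opening paragraph justifies the trial partly by the absence of safety evaluations of rapid correction.

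**The concern.** A trial that sets out to compare the safety of two ways of giving the same fluid should collect harms without first asking whether they come through one chosen mechanism. Here the stated rule asks that first. Overcorrection is the primary outcome, so adverse events collected because they relate to overcorrection largely restate the primary result. Harms that arise from the mode of delivery itself, and do not pass through overcorrection, could differ between arms and leave no trace in the recorded events.

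The order of steps adds a second problem. If relatedness is judged before an event is written down, an event judged unrelated is never recorded and nobody can review the judgement. In an open-label trial that judgement may be made by people who know the arm. A later safety statement about either regimen would then rest on an unknown denominator of unrecorded events.

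**Working it through.** The plan gives no figure on this point, so the check is a comparison of its sections, followed by two small calculations for context.

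**1. Which events have a stated route into the data?**

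| Type of event | Stated route | Where |
|---|---|---|
| Related to overcorrection, any severity | Recorded and followed up | Safety issues |
| Serious, any cause | Reported to investigators and the Ethics Committee | Safety issues |
| Unanticipated, any cause | Reported to the Institutional Review Board | Data and safety monitoring |
| Persisting symptoms, reduced consciousness, slow sodium rise | Secondary outcomes in all patients | Outcome measures; Statistical analyses |
| Complication of relowering | Can be read as related to overcorrection | Safety issues |
| Non-serious, expected, not attributed to overcorrection | None stated | – |

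Only the last row is empty. The second and third rows describe reporting for oversight; the article states no between-group analysis of those reports.

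**2. Could events in the empty row differ by arm?** The inputs are the starting regimens in the two treatment-group sections.

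- Bolus, moderately severe: 2 mL/kg over 20 min = 2 × 60/20 = 6 mL/kg/h while running.
- Bolus, severe: 4 mL/kg over 40 min = 4 × 60/40 = 6 mL/kg/h while running.
- Continuous: 0.5 mL/kg/h (moderately severe) or 1 mL/kg/h (severe).
- Ratio of initial delivery speed: 6/0.5 = 12 and 6/1 = 6.

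The arms thus differ 6- to 12-fold in initial delivery speed. This shows only that infusion-related events could plausibly differ by arm; it says nothing about their rate or about which regimen is better.

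**3. Is the filter defined?** The article does not define what counts as related. Its sodium thresholds do not settle the matter either: the primary outcome uses a rise above 12 mmol/L in the first 24 h, while Safety issues places its overcorrection check beside relowering at 10 mmol/L or more in that period. Which of these, if either, governs an event's relatedness is not said.

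**4. What would recording gain?** If a harm is collected and none is seen in an arm of n patients, the one-sided 95% upper limit for its rate is 1 − 0.05^(1/n).

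- n = 89 (planned per arm): 1 − 0.05^(1/89) = 3.3%.
- n = 75 (89 × 0.85 = 75.65, after the planned 15% dropout): 1 − 0.05^(1/75) = 3.9%.

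If the harm is not collected, an empty record supports no limit at all.

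**The case against.** The strongest reply is that the remaining gap is narrow. The rule does not contain the word only, and serious and unanticipated events of any cause are reported. Serious events also go to the investigators, who could count them by arm. Undercorrection, which the Background names as the opposite danger ("whereas undercorrection may be insufficient to prevent its life-threatening manifestations"), would show in symptoms, GCS and time to sodium rise, all compared by arm. A journal article also leaves case-report forms and safety tables to fuller documents.

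Most of this stands, and it rules out several stronger readings that a reader might infer:

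- *Nothing but overcorrection events is captured, so no other harm of either regimen can appear.* The serious and unanticipated reporting and the secondary outcomes contradict this.
- *Relowering complications are excluded.* Relowering is presented as the response to overcorrection, so its complications can fall under the rule, and its incidence is compared by arm.
- *Recorded events cannot exceed the overcorrection rate, so most patients are shut out.* At the planning rates, 0.20 × 89 + 0.05 × 89 = 22.25 patients overcorrect, leaving 155.75 of 178 (87.5%). That is merely the planned share without the primary outcome. The recording rule is not tied to that definition, a patient may have several events, and serious and unanticipated events lie outside any such cap.

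The argument from condensation does not carry. The article is not silent on scope; it states one. If a fuller document is broader, this sentence misstates it and still needs correcting. GCS and symptom changes at 24 and 48 h, and length of stay, do not identify an infusion or fluid-load event.

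**Conclusion.** The point holds in limited form. As written, non-serious, expected adverse events not attributed to overcorrection have no stated route into the data, and an undefined attribution step comes before recording. The safety comparison is therefore incomplete and leans towards the mechanism of the primary outcome.

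No numerical size can be given, since the article reports no rate for such events, and no direction of bias can be claimed. The primary outcome, a laboratory measure, is untouched. This is a worthwhile and inexpensive improvement, not a threat to the main result.

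The conclusion rests on two assumptions: that sites follow the sentence as worded, and that those judging relatedness know the arm. The second is inferred from the open-label design; the article does not say who makes the judgement.

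**What to change.** Reword the rule in Safety issues so that all adverse events in all randomized patients are recorded over the study period, regardless of presumed cause. Make relatedness to overcorrection a separate field completed after the event is recorded, with a written definition and, where feasible, assessed without knowledge of the arm. State that all events, serious events and the related subset will be tabulated by arm.

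The table should be descriptive. With 89 per arm, power to separate assumed rates of 10% and 20% is about 46%, and of 5% and 15% about 61%, so estimates with intervals are more useful than tests.

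The cost is modest extra data entry over a 48-h treatment period in which sodium is already measured every 6 h and all fluids are monitored. No treatment rule changes. Events left unrecorded may not be recoverable later, so the change is worth making as early in recruitment as possible.

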### Sample size calculation

In the medical literature, ODS is a critically important outcome, but the incidence of ODS is very low [1, 15, 31]. Therefore, as a surrogate marker of ODS, the rate of overcorrection >12 mmol/L within 24 h or >18 mmol/L within 48 h was calculated for the primary study outcome. A previous study reported that the overcorrection rate was 10–16% with slow continuous correction of hyponatremia [10]. However, there was insufficient information for estimating the rate of overcorrection with intermittent bolus infusion. Based on clinical practice and experience, we estimated that the overcorrection rate was 32% with slow continuous correction during a recent 1-year period. We therefore expect that the rate of overcorrection will be 5% in patients treated with rapid intermittent correction and the rate of overcorrection with slow continuous correction could be as high as 20%. We calculated the required sample size for an estimated dropout rate of 15%, a two-sided level of significance of *α* = 5%, a power of 80%, and found that 89 participants will be required in each group to find a significant difference using a *χ*
^*2*^ test. A total of 178 participants will be included in the analysis. We have considered one interim analysis at the time that a half of subjects complete the study. The O’Brien-Fleming’s alpha spending function will be used to test the first interim and final analysis of primary outcome.

### Statistical analyses

Statistical analyses will be performed on both per-protocol (PP) and intention-to treat (ITT) bases. For the PP analysis, all participants who completed the study will be included to evaluate the primary and secondary outcomes. For the ITT analysis, all participants who were enrolled and randomized to one of the two groups will be included. The baseline characteristics and laboratory data will be presented as means and standard deviations for continuous variables and as frequencies and percentages for categorical variables.

The incidence of overcorrection, ODS, relowering treatment, and target correction rate (achieved sNa <10 mmol/L within the first 24 h and sNa <18 mmol/L within 48 h) will be compared between the two groups using a *χ*
^*2*^ test and Fisher’s exact test. In interim analysis, if the *P* value < 0.003 then we would stop the study early for significance of outcome. If not, we would recruit another half of subjects. The differences in changes in symptoms and GCS scores between pretreatment and 24 and 48 h, time to reach target sNa, time to achieved sNa ≥5 mmol/L for the first time, and length of hospital stay will be analyzed using Student’s *t* test or the Mann-Whitney *U* test. A value of *P* < 0.05 will be considered statistically significant. All analyses will be performed using SPSS Statistics software V21.0 (IBM Corporation, Armonk, NY, USA).

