### Randomization

A research coordinator will perform the randomization. A list of random numbers will be generated by an independent statistician. Eligible participants will be randomly assigned 1:1 to either the slow continuous correction group or the rapid intermittent correction group in accordance with the predefined randomization list with a block size of 2. Randomization will be stratified based on the symptom severity related to hyponatremia (moderately severe or severe).

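### The primary comparison leaves out the severity strata used in randomization and names no deciding test or analysis set; the power cost is small, but the open choice can reverse a verdict

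*Protocol article*

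**What the plan says.** **Design.** The Randomization section of the protocol article says: "Randomization will be stratified based on the symptom severity related to hyponatremia (moderately severe or severe". The section on practical treatment guidelines adds that the infusion rate of 3% saline depends on severity within each arm.

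**Analysis sets.** Statistical analyses opens with "Statistical analyses will be performed on both per-protocol (PP) and intention-to treat (ITT) bases". ITT is everyone randomized. The other set is defined by completion: "For the PP analysis, all participants who completed the study will be included to evaluate the primary and secondary outcomes". Neither is called primary.

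**Tests.** In the same section, four outcomes (overcorrection, ODS, relowering treatment and target correction rate) "will be compared between the two groups using a" chi-square test and Fisher's exact test. There is no stratum term and no rule for choosing between the tests. The interim threshold of P < 0.003 follows, with no test or set attached. GCS changes are compared by t test or Mann-Whitney test, although GCS is recorded before treatment.

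**Sample size.** The Sample size calculation section names chi-square alone: "89 participants will be required in each group to find a significant difference using a" chi-square test. The Discussion plans a look at each severity level, but only at the interim.

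**The concern.** Two separate matters arise.

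1. **The deciding P value is open.** Two tests and two sets are listed side by side for the primary outcome. In an open-label trial with an efficacy stop, the test and set behind the P value should be fixed before any data are compared. Otherwise a result near the boundary depends on which one is quoted.

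2. **The analysis does not follow the randomization.** If severity predicts overcorrection, stratified randomization balances it between the arms. A test that ignores the strata then overstates the variance of the difference, so it becomes conservative and gives away some power.

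The completer definition adds a smaller problem. It keeps patients treated outside the protocol, whom the Discussion anticipates because staff work in shifts, and it excludes patients on an event after randomization. It is therefore not a per-protocol set in the usual sense.

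**Working it through.** **Inputs from the Sample size calculation section.** "We therefore expect that the rate of overcorrection will be 5% in patients treated with rapid intermittent correction"; "the rate of overcorrection with slow continuous correction could be as high as 20"%; "an estimated dropout rate of 15%, a two-sided level of significance of" 5%; power 80%.

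**Step 1: reproduce the plan's figure.** Pooled-variance formula, no continuity correction, mean rate 0.125:

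n = [1.960 × √(2 × 0.125 × 0.875) + 0.8416 × √(0.20 × 0.80 + 0.05 × 0.95)]² / 0.15² = (0.9167 + 0.3834)² / 0.0225 = 75.12 per group.

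75.12 / 0.85 = 88.4, rounded up to 89. The stated 89 is reproduced. It is an unstratified, uncorrected chi-square calculation.

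**Step 2: chi-square against Fisher, exact binomial enumeration at 5% versus 20%.**

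| Per arm | Chi-square power | Fisher power | Opposite verdicts |
|---|---|---|---|
| 75 | 82.7% | 76.0% | 6.8% |
| 89 | 88.7% | 84.3% | 4.4% |

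(89 × 0.85 = 75.65, hence 75 evaluable per arm if all the planned dropout is lost.)

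**Step 3: single tables.** With equal arms of n, and a and b events, chi-square = (a − b)² / [t(2n − t)/(2n)], where t = a + b.

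- Final, 12/89 versus 4/89: 64 / (16 × 162/178) = 4.40, P = 0.036. Fisher P = 0.064.
- Interim, 11/44 versus 1/44 (178/2 = 89 patients, so 44 or 45 per arm): 100 / (12 × 76/88) = 9.65, P = 0.0019. Fisher P = 0.0035. One test stops the trial at 0.003 and the other does not. At the planned rates the two disagree on stopping in 4.1% of trials.

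**Step 4: two tests by two sets.** Assume 15% random non-completion and 89 per arm, 40,000 runs. At 5% versus 20%, the four P values do not all agree at 0.05 in about 13% of trials if dropouts' outcomes are known, and in 8.5% if missing counts as no event. With 12.5% in both arms, quoting whichever of the four is smallest gives a type I error of about 6.7% or 5.6% respectively.

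**Step 5: stratified against unstratified.** The documents give neither the severe share nor any rate by stratum, so these are assumptions. The Cochran-Mantel-Haenszel (CMH) statistic is z = Σ(a_s − t_s/2) / √Σ[m_s² t_s(2m_s − t_s) / ((2m_s)²(2m_s − 1))], with m_s patients per arm in stratum s. Overall rates are held at 5% versus 20%, by simulation with at least 200,000 runs per row.

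| Assumed severe:moderate rate ratio | Rates, bolus; continuous (moderate/severe) | Unstratified power | CMH power |
|---|---|---|---|
| 1 (25% severe, 76 per arm) | 5/5; 20/20 | 83.3% | 83.1% |
| 2 (25% severe, 76 per arm) | 4/8; 16/32 | 83.4% | 83.5% |
| 3.7 (25% severe, 76 per arm) | 3/11; 12/44 | 84.2% | 85.5% |
| 4 (50% severe, 76 per arm) | 2/8; 8/32 | 84.0% | 85.0% |
| 6 (30% severe, 75 per arm) | 2/12; 8/48 | 84% | 87% |

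Type I error of the unstratified test is 5.0% if severity is not prognostic, 4.9% at 10%/20% in both arms, 4.2% at 7.5%/27.5%, 3.5% at 5%/35% (50:50 split) and 2.8% at 8%/48%. CMH stays between 4.8% and 5.0%.

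**The case against.** The best defence is that the plan hangs together. The trial is sized on an unstratified chi-square test and lists that test for the analysis. The phrase that adds Fisher covers four outcomes, one of which is ODS, and the sample size section itself describes ODS as very rare. The ordinary reading is chi-square, with Fisher for sparse tables. At a pooled rate of 12.5% the smallest expected cell is 9.4 with 75 per arm, 11.1 with 89 and 5.5 with 44, so the usual sparse-table rule would not send the primary outcome to Fisher. A separate analysis plan may also name the primary set.

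Most of this stands. It rules out reading the four P values as having equal standing. It does not close the gap: the article gives no rule for choosing a test, lists both sets without ranking them, and ties the interim stop to neither.

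Two stronger readings are also tempting.

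- **That ignoring the strata pulls power down to 75%.** A simulation does give 75% against 80% for CMH, with 30% severe, control rates of 8% and 48%, and a common odds ratio of 0.21. But that odds ratio implies bolus-arm rates of 1.8% and 16.2%, or 0.7 × 1.8 + 0.3 × 16.2 = 6.1% overall instead of the planned 5%. Keeping 5% versus 20% in the same strata gives 84% against 87%. The fall below 80% comes from the smaller treatment effect.
- **That Fisher's test fails the stated 80% power.** Its 76% applies only at 75 evaluable per arm. At 89 per arm it is 84%, and the article says all 178 will be analysed.

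It is also fair to object that a set defined by protocol deviations, like one defined by completion, selects on events after randomization. That is why it should only be supportive. Change-score comparisons of GCS are valid under randomization, so baseline adjustment is an efficiency gain and not a correction.

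**Conclusion.** The point holds in two parts of unequal weight.

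**The open choice of test and set is the part that matters.** Plausible tables give opposite verdicts at the final analysis and at the interim stop. Chi-square and Fisher disagree in about 4% to 7% of trials at the planned rates. Across both tests and both sets the figure is about 8.5% to 13%, assuming 15% random non-completion. The type I error of 5.6% to 6.7% is what unrestricted choice would produce; nothing in the article says the choice will be made that way.

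**Omitting the strata is a modest and conditional loss.** It does not make the test invalid or inflate type I error, and 89 per group remains adequate. The power lost is about 0 if severity is not prognostic, about 0 to 1.4 points for rate ratios up to about four-fold, and about 3 points at an extreme six-fold ratio with 30% severe, where type I error under the null falls to 2.8%. All stratum shares and rates behind these figures are assumed. A prognostic effect is plausible, because severity sets the starting infusion intensity, but the documents do not show one.

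**What to change.** - Name ITT as the primary set, and a Cochran-Mantel-Haenszel test stratified by symptom severity as the primary test. Report a stratified risk difference with its 95% CI.
- State that the same test and set supply the P value at the interim and final looks.
- Reserve Fisher's exact test for sparse outcomes such as ODS.
- Make the per-protocol analysis supportive, and define its set by absence of major protocol deviations, with completion no longer the criterion.
- As a secondary improvement, analyse GCS at 24 and 48 h adjusting for baseline GCS and severity stratum (ANCOVA or an ordinal model).

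The cost is wording in the analysis section. No new data are needed, and the sample size stays at 89 per group. If severity proves not to be prognostic, stratifying costs about 0.2 points of power (83.1% against 83.3%).
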